## 4. Objective and assumptions

**The general objective** of the project is to validate the new CAD/CAM brace design method integrating the optimization of immediate correction.

**Primary Hypothesis (H1)** : After 1 year and 2 years of use, the out-of-brace correction, as measured by Cobb's angle, from the Test braces will be non-inferior to the Control braces. The non-inferiority margin will be 5 degrees.

**Secondary hypothesis (H2)** : The immediate and medium-term (1 and 2 years) failure rate of treatment will be 10% lower for Test braces compared to Control braces. There are three different types of failures:

1. Mid-term failure (1 and 2 years) – relative progression : A progression of the out-of-brace Cobb angle of 5 degrees or greater than the value measured at visit 1.
2. Intermediate (study duration) failure – absolute progression : A progression of the Cobb angle of the main off-brace curvature to greater than 45 degrees (SRS failure criterion).
3. Medium-term failure (duration of the study) – surgery : Stopping treatment with a brace and a decision to have surgery (AVBGT or fusion).

**Secondary hypothesis (H3)** : The quality of life of patients wearing Test braces in the medium term, as measured with the SRS-22r questionnaire, will be non-inferior to that of patients wearing control braces. The non-inferiority margin will be 10%.

**Secondary hypothesis (H4)** : The immediate in-brace correction of the Cobb angle of the Test brace will be no less than that of the control brace. The non-inferiority margin will be 5 degrees.

The effects measured (dependent variables) are as follows:

| Effects measures                                                         | Descriptions                                                                           |
|--------------------------------------------------------------------------|----------------------------------------------------------------------------------------|
| Major                                                             |                                                                                        |
| Cobb angle off brace (Initial, 6 months, 1 year, 2 years).               | Measure using low-dose EOS radiography to assess the evolution of scoliosis.           |
| Secondary                                                         |                                                                                        |

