| Cobb angle in the brace. (Initial)                                       | Measure using digital radiography to assess the immediate corrective effect of braces. |
| Treatment failure rate (Initial, 6 months, 1 year, 2 years)              | See failure criteria in section 6.5                                                    |
| The lordosis and kyphosis effect of the brace (Initial, 1 year, 2 years) | The angles of the curves in the sagittal plane will be measured on the x-ray images.   |
| The number of hours wearing the brace per day (Initial, 1 year, 2 years) | A compliance monitor will measure the rate of brace use.                               |
| The patient's quality of life (Initial, 6 months, 1 year, 2 years)       | The quality of life of patients will be calculated from the SRS-22r questionnaire      |

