## **6. Methodology**

### **6.1. Study design**

A prospective, double-blind, non-inferiority, controlled and randomized clinical trial will be conducted to assess the effectiveness of a new orthopedic brace design platform. Fifty-eight patients will be recruited at the CHU Ste-Justine orthopedic clinic. The study will be divided into two phases. The first phase will use a crossover design to assess the immediate correction of both types of brace. The second phase will use a parallel design with a 1:1 allocation to assess the mid-term correction.

In phase 1, each patient will try on each type of brace with a “control: test” or “test: control” trial sequence. Immediate correction in braces will be assessed. During phase 2 each patient will use one of the two types of braces for a period of two years. There will be a renewal of the brace after 6 or 12 months based on updated spine x-rays and a new trunk geometry. This is in order to consider the growth of the patient and the inherent changes in the patient's body and the scoliotic deformity. Taking into account that all patients do not follow the same growth, renewal of the brace may sometimes be necessary before 12 months (for example after 6 months following a rapid growth spurt). In this case, the brace will be renewed before the end of 12 months to ensure adequate follow-up of the treatment by the patient. If the patient is part of the test group, the optimization of the correction will be redone.

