### **6.5. Failure criteria**

The failure criteria for the treatments are those mentioned in secondary hypothesis H2.

Note that a patient in phase #1 is likely to have immediate failure of the brace assigned to them for phase #2. In this case, for ethical reasons, the brace of the other group will be assigned to him. Also for ethical reasons, a patient may have to use the brace of the other group during phase #2 if it offers an immediate correction of the Cobb angle greater than 5 degrees.

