#### 8.4. Analysis of secondary hypothesis H2

The analysis of secondary hypothesis H2 will have the treatment failure rate as the dependent variable and the type of brace worn as the independent variable. The incidence of failures will be presented with a Kaplan-Meier curve, the statistical analysis will be done with a log-rank test.

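### H2 includes an immediate failure rate at the visit where every patient tries both braces, but 8.4 gives all of H2 one log-rank test by brace worn, which cannot use the paired results

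*Protocol*

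**What the plan says.** - **H2 (Protocol, section 4)** covers two time frames: "The immediate and medium-term (1 and 2 years) failure rate of treatment will be 10% lower for Test braces compared to Control braces". It then says "There are three different types of failures" and lists off-brace progression from Visit 1, an off-brace main curve above 45 degrees, and a decision for surgery. All three are labelled as mid-term, intermediate or over the study duration.
- **Effects table (section 4)** has the row "Treatment failure rate (Initial, 6 months, 1 year, 2 years" and sends the reader to 6.5 for the criteria.
- **Section 6.1** makes phase 1 a crossover: "In phase 1, each patient will try on each type of brace". The quantity assessed is in-brace correction. Section 6.4 (Visit 2) obtains it from a supine film in each brace.
- **Section 6.5** refers back to H2 for the criteria, then expects that the brace assigned for phase 2 may fail immediately in phase 1: "In this case, for ethical reasons, the brace of the other group will be assigned to him".
- **Section 8.4** says that the H2 analysis "will have the treatment failure rate as the dependent variable and the type of brace worn as the independent variable", with a Kaplan-Meier curve and a log-rank test. No other H2 analysis is given.
- **Section 8.6 (H4)** is the only analysis section that recognises the crossover.

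**The concern.** A log-rank test compares independent groups over follow-up. Immediate failure would arise at Visit 2, before phase 2 follow-up starts, and could be assessed for both braces in the same patient. Putting it into the 8.4 analysis has two consequences.

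1. Each patient contributes one brace, so the result for the other brace and the within-patient comparison are unused.
2. The grouping variable interacts with 6.5. A patient whose assigned brace fails immediately moves to the other type. If 'worn' means worn in phase 2, the failed brace is not the one analysed unless the other brace failed as well.

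At stake is the immediate component of H2. Its test would be less precise than the design allows and, on the second reading, biased toward no difference.

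**Working it through.** **Figure in the plan.** There is no rate, power or event count for H2. The only sized hypothesis is H1. Its 25 per group reproduces with margin 5, SD 7, one-sided 5% and 80% power: 2 × (1.645 + 0.842)² × 49 / 25 = 24.2, rounded up to 25. It does not bear on this point beyond supplying 29 per group and 58 in total (section 8.1).

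**Assumptions.** Immediate failure pC = 20% (control) and pT = 10% (test), reading H2's 10% as absolute points, which the protocol does not specify. Within-patient correlation r is 0 to 0.5. Allocation is 1:1, and only the switch after immediate failure is applied. None of these rates or correlations comes from the documents.

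**Step 1. Probability that both braces fail.** p11 = pC·pT + r·√[pC(1−pC)·pT(1−pT)] = 0.02 + 0.12r. This gives 0.02 (r = 0), 0.056 (r = 0.3) and 0.08 (r = 0.5).

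**Step 2. Grouped by brace worn after the switch.**
- Share wearing control: ½[(1−pC) + pT] = ½ × 0.9.
- Share wearing test: ½[(1−pT) + pC] = ½ × 1.1.
- In each group the worn brace has failed only in patients who switched and in whom both failed, a share of ½·p11.
- Recorded rates are therefore p11/0.9 (control) and p11/1.1 (test).
- r = 0: 2.2% and 1.8%, difference 0.4 points.
- r = 0.5: 8.9% and 7.3%, difference 1.6 points.
- The assumed true difference is 10 points.

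**Step 3. Precision if grouped as randomised, against paired.**
- Unpaired, 29 against 29: SE = √[(0.16 + 0.09)/29] = 9.3 points.
- Paired in 58: SE = √[(p10 + p01 − 0.10²)/58], with p10 = 0.20 − p11 and p01 = 0.10 − p11.
- r = 0: √(0.25/58) = 6.6 points. r = 0.3: √(0.178/58) = 5.5 points. r = 0.5: √(0.13/58) = 4.7 points.
- The paired SE is 29% to 49% smaller.

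**Step 4. Other assumed rates.** The test rate is 10 points below control throughout, and power is at two-sided 5%. The share counted as worn is p11/(pC + pT). Grouped as randomised, the expected share is 50% in every row. Ranges run from r = 0 to r = 0.5 in the second column and in the last.

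| Control / test | Share of brace-level failures counted, as worn | Power, 29 vs 29 | Power, exact McNemar, 58 pairs |
|---|---|---|---|
| 15% / 5% | 3.7–23.2% | 24.2% | 31.5–50.3% |
| 20% / 10% | 6.7–26.7% | 18.3% | 23.9–40.5% |
| 30% / 20% | 12.0–30.3% | 13.8% | 17.1–29.9% |
| 40% / 30% | 17.1–33.2% | 12.1% | 14.5–25.7% |

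**Step 5. Can a listed criterion be scored at Visit 2?** The first type is "A progression of the out-of-brace Cobb angle of 5 degrees or greater than the value measured at visit 1". The second also uses the off-brace curve, and the third is a decision to operate. The Visit 2 films are taken in the brace. None of the three can be scored separately for each brace from those films, and 6.5 adds no further criterion.

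**The case against.** The strongest reply is that phase 1 measures the in-brace Cobb angle, not failure. A reader might infer from H2, the table and 6.5 that the trial already records an immediate failure result for each brace in all 58 patients. It does not, because no criterion exists, and a paired test has no outcome until one is written. This stands. It does not rescue 8.4, however: any Visit 2 criterion scored in each brace gives paired data, so a definition alone would leave the wrong test in place.

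Second, a reader might conclude that 8.4 certainly discards most immediate failures and forces the result to no difference. That follows only if 'worn' means worn after the switch. The same wording is used for H1 and H3 and may simply label the treatment factor. Section 8.2 also plans an intention-to-treat analysis of all randomised patients. Grouped as randomised, half of the brace-level failures are expected to be counted and the expected difference is unbiased. But 8.2 does not say that patients are grouped as randomised, and even then the pairing is lost. Events at time zero are not in themselves invalid in a log-rank test.

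Third, H4 already compares immediate correction within the crossover, on a continuous scale that would normally carry more information than a dichotomy. That is true, and it is why dropping the immediate part of H2 is a reasonable alternative. But H4 concerns the angle, not the failure rate that H2 claims to compare.

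Finally, a separate statistical analysis plan might treat this differently. Section 8.4 nevertheless names both the test and the grouping variable, so the point concerns a stated method, not an omitted detail.

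**Conclusion.** The point holds for the immediate component of H2. The single log-rank analysis does not fit data that would be paired at Visit 2. It leaves at least half of the brace-level results and the pairing unused. On the as-worn reading it counts only patients in whom both braces fail: about 4% to 33% of brace-level failures over the assumed rates, with an assumed 10-point difference recorded as 0.4 to 1.6 points at 20% against 10%. Grouped as randomised, the loss is one of precision: a standard error of 9.3 points against 6.6 to 4.7 paired.

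These sizes are illustrations. They rest on assumed rates and correlations, on an absolute reading of the 10%, and on leaving out the second 6.5 rule, which allows a switch when the other brace corrects better by more than 5 degrees. Even paired, exact power is only about 15% to 50%, so the gain is real but modest. H1 is not affected by this point. The passages also disagree on whether an immediate failure exists at all, and that must be settled together with the analysis.

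**What to change.** Reconcile H2, the failure-rate row of the effects table, 6.5 and 8.4 in one of two ways.

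- **(a) Keep immediate failure.** The investigators state the criterion. Section 8.4 then analyses it as paired binary data in all patients, by the brace tested at Visit 2 and before any switch: paired difference in proportions, 95% confidence interval and exact McNemar test. The Kaplan-Meier and log-rank analysis of medium-term failure starts at brace delivery and, for the intention-to-treat analysis, groups patients by randomised brace.
- **(b) Drop it.** Remove 'immediate' from H2 and 'Initial' from the failure-rate row, reconcile 6.5 with that change, and leave the immediate comparison to the crossover analysis of H4.

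Either way the text should say whether 10% lower is absolute or relative. The cost is wording in four places, plus one short paired analysis under (a). No new visits, films or patients are needed.

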## 8. Statistical analysis plan

### 8.1. Sample size justification

The sample size was calculated to be able to accept the main hypothesis (H1) with a probability of 5% of committing the type I error and a power of 80%. The calculation was performed with nQuery software (GraphPad Software DBA Statistical Solution, San Diego, CA) and the following parameters were used:

- Significance level  $\alpha = 5\%$
- Allocation ratio  $k = 1$
- Margin of non-inferiority  $\delta = 5^\circ$
- standard deviation  $\sigma = 7^\circ$ 
- Power  $(1 - \beta) = 80\%$

The sample size should be 25 per group, so a total of 50 patients. On the other hand, a loss to follow-up of 15% is anticipated. We will therefore need 29 patients per group for a total of 58 patients.

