#### 8.5. Analysis of secondary hypothesis H3

The analysis of secondary hypothesis H3 will have the respective scores of the SRS-22r questionnaire as the dependent variable and the type of brace worn as the independent variable. The 95% confidence interval of the difference in score between the test brace and the control brace will be constructed and compared to the non-inferiority margin.

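### The H3 quality-of-life margin is 10% of an unstated base, while section 8.5 compares it with a confidence interval in score units, so the protocol does not determine the threshold for H3

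*Protocol*

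**What the plan says.** Three places in the protocol bear on this.

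- **Section 4, H3.** Medium-term quality of life, measured with the SRS-22r, "will be non-inferior to that of patients wearing control braces. The non-inferiority margin will be 10" per cent. No base is given for the percentage.
- **Section 4, table of effects.** "The quality of life of patients will be calculated from the SRS-22r questionnaire", with assessments at the initial visit, 6 months, 1 year and 2 years. The scale range, scoring and SD are not given.
- **Section 8.5.** The H3 analysis "will have the respective scores of the SRS-22r questionnaire as the dependent variable". The decision rule follows: "The 95% confidence interval of the difference in score between the test brace and the control brace will be constructed". That interval is then set against the H3 margin.

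For contrast, H1 and H4 each carry the statement "The non-inferiority margin will be 5 degrees", and the outcome in both is a Cobb angle in degrees.

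**The concern.** A difference in score is measured in points, and the margin is a percentage. The two can be compared only after the percentage has been turned into points, and that needs a base. At least three bases are natural: the range of the scale, its maximum, or the control-group mean. Each gives a different margin, and the protocol chooses none of them.

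The outcome is open as well. Section 8.5 refers to scores in the plural, while H3 makes one quality-of-life claim with one margin. A reader cannot tell which score the claim rests on.

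At stake is the conclusion on H3, the only patient-reported hypothesis in the trial. Section 9.1 itself lists lower comfort of the optimized brace as a risk. If the same data can be declared non-inferior or not according to how the 10% is read, the H3 result will be hard to defend.

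**Working it through.** **1. The plan's own figure.** The protocol sizes only H1, "with a probability of 5% of committing the type I error and a power of 80"%, with margin 5° and SD 7°. With one-sided alpha 0.05, n = 2σ²(z₀.₉₅ + z₀.₈₀)²/δ² = 2 × 49 × (1.645 + 0.842)²/25 = 24.2, so 25 per group, as stated. This neither supports nor refutes the point on H3. It supplies the 25 evaluable patients per group used below. No power is claimed for H3.

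**2. Assumptions, none of them in the document.** The score is a mean on a 1 to 5 scale on which higher is better. The SD is 0.5, with a range of 0.4 to 0.6. The control mean lies between 3.5 and 4.5. The interval is the two-sided 95% interval that section 8.5 names.

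**3. What 10% could mean.**
- Of a control mean of 3.5 to 4.5: 0.35 to 0.45 points.
- Of the range (5 − 1 = 4): 0.40 points.
- Of the maximum (5): 0.50 points.

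**4. Half-width of the interval.** t₀.₉₇₅ with 48 df is 2.011. Half-width = 2.011 × SD × √(2/25), which is 0.227 at SD 0.4, 0.284 at SD 0.5 and 0.341 at SD 0.6.

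**5. Power at no true difference.** This is the probability that a noncentral t with 48 df and noncentrality m/(SD × √(2/25)) exceeds 2.011, where m is the margin. The worst observed difference (test minus control) that still passes is −(m − half-width).

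| Base of the 10% | Margin | Power, SD 0.4 | Power, SD 0.5 | Power, SD 0.6 | Worst passing difference, SD 0.5 |
|---|---|---|---|---|---|
| Control mean 3.5 | 0.35 | 86% | 68% | 52% | −0.07 |
| Range 4 (or control mean 4.0) | 0.40 | 93% | 79% | 64% | −0.12 |
| Control mean 4.5 | 0.45 | 97% | 88% | 74% | −0.17 |
| Maximum 5 | 0.50 | 99% | 93% | 82% | −0.22 |

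**6. One data set, several verdicts.** Take an observed loss of 0.15 points.
- SD 0.5: lower limit −0.15 − 0.284 = −0.434. Fails at 0.35 and 0.40, passes at 0.45 and 0.50.
- SD 0.4: lower limit −0.377. Fails at 0.35, passes at the other three.
- SD 0.6: lower limit −0.491. Passes only at 0.50.

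At SD 0.5 the verdict depends on the reading for any observed loss between about 0.07 and 0.22 points.

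**The case against.** The strongest reply is that a statistical analysis plan may exist and could name the base before any score is seen, since such details are often left to it. That limits the point without removing it. The protocol does not leave the matter open: it fixes a margin in section 4 and a decision rule in section 8.5, and the units do not match. An analysis plan could only choose among readings that the protocol permits.

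A reader might infer four stronger things, which the document does not support.

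- **That the conversion will be chosen after the data are seen.** Nothing shows this. The protocol shows only that it does not fix the conversion.
- **That the comparison is impossible.** It is not. Once a base is named, one multiplication gives the margin in points. This is an ambiguity.
- **That a margin tied to the observed control mean makes the interval seriously wrong.** The matching contrast is test mean − 0.9 × control mean, with variance factor 1 + 0.81 = 1.81 against 2 for a plain difference. The effective critical value is 1.96 × √(2/1.81) = 2.06, a one-sided error of 2.0% instead of 2.5%. That is slightly conservative and negligible.
- **That several scores are tested and any one can carry H3, inflating the error rate.** No such rule appears, nor any number of scores. The plural in section 8.5 may mean domains, but it could also mean groups or visits, and its next sentence uses the singular.

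It is also fair to say that every SRS-22r figure above is assumed, that the 0.15-point example is one point within a band, and that the power figures contradict no claim in the protocol.

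**Conclusion.** The point holds as a defect in how the H3 rule is written. The margin is a percentage of an unstated base, the interval is in score units, and the deciding score is not named, so this document does not determine the threshold for H3.

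That conclusion needs no assumptions. Its size does: with the scale, control means and SD 0.5 assumed above and 25 per group, the readings differ by up to 0.15 points in the margin (0.35 to 0.50) and 25 percentage points in power (68% to 93%). That is enough to reverse the verdict on plausible data. A different SD shifts the band of observed losses affected but does not remove it.

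The consequence is limited to one secondary hypothesis. The H1 conclusion and the sample size are unaffected.

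**What to change.** Before any outcome data are compared, amend H3 in section 4 and the rule in section 8.5 to state:

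- the margin in SRS-22r points, with the base from which it is derived;
- the one SRS-22r score that decides H3;
- the deciding time point or points, consistent with the medium term as section 4 uses it under H2 (1 and 2 years), and, if both are named, whether both must pass;
- the rule: H3 is met if the lower limit of the 95% confidence interval for test minus control lies above minus the stated margin.

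Optionally, the interval can be adjusted for the Visit 1 SRS-22r score, which is already collected, to gain precision. The unit problem does not require this.

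The cost is a wording change, with no new patients, visits or data. The small downside is that the remaining SRS-22r scores become supportive.

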## 5. Descriptions of braces

This section describes the two different types of brace, control brace and test brace, which will be used.

### 5.1. Control Brace

The control brace will be made using the method currently used at Sainte-Justine Hospital. It will therefore be designed by an experienced orthotist using scanning of the patient's skin's outer surface, and Rodin4D, a 3D design platform. The brace will be adapted to include a compliance monitor. The compliance monitor is an iButton thermal sensor ( *Boston Brace, MA, USA* ), this will record the wearing time of the brace. This will in no way affect the correcting effect of the

brace. It will then be manufactured by thermoforming in the facilities of Orthèse-Prothèse Rive-Sud.

